## Study design

This is a prospective phase IV clinical trial for evaluating the humoral and cell-mediated immune responses in population groups to be vaccinated with the avian influenza vaccine according to the national recommendations in Finland.

The study is observational in nature as no vaccines are allocated or administered through this study protocol. However, blood and saliva samples are obtained to evaluate vaccine immunogenicity, and thus, the study is defined as an intervention study according to the EU regulation on clinical trials (536/2014). In the study, only licensed vaccines given within the framework of the national vaccination program/campaign are monitored, which have been given in accordance with the national vaccination campaign. In addition, the blood and saliva samples collected in the study do not pose more than minimal additional risk or burden to the safety of the subjects compared to normal clinical practice. Therefore, this study is a low-intervention trial. No control arm is included in this study.

## Investigational products

The currently available zoonotic influenza vaccine, AFLUNOV, is based on the A/turkey/Turkey/1/2005 (H5N1) vaccine strain. The vaccine contains 7.5 µg of H5 hemagglutinin antigen and MF59C.1 adjuvant containing squalene and polysorbate. The AFLUNOV vaccine is licensed for all adults 18 years of age or older. The vaccine is given as a series of 2 doses at least 21 days apart (3 weeks) by intramuscular injections according to the marketing authorization. The manufacturer of AFLUNOV vaccine, Seqirus S.r.l., has 9.10.2023 received marketing authorization for the medicinal product Zoonotic Influenza Vaccine Seqirus, based on the same strain. Seqirus S.r.l., has applied for authorization for an updated composition, which is based on the A/Astrakhan/3212/2020 (H5N8) strain [10]. The updated zoonotic influenza vaccine [4] will be evaluated as the investigational product under this protocol. Seasonal influenza vaccine in the national vaccination program will be evaluated as well. The vaccine in the national vaccination program for the season 2023-2024 is VaxigripTetra, manufactured by Sanofi.

## Study participants

The study participants will include subjects aged 18 to 65 years who belong to the target groups for avian influenza vaccination (part of which have previously received an avian influenza vaccine) or who have provided samples for evaluation the immunity against influenza and other vaccine preventable diseases.

### Cohort 1

Study subjects for cohort 1 will include subjects who belong to the target groups for which the avian influenza vaccine will be recommended as part of the national H5N1 vaccination campaign (targeted sample size 300). These groups can include but are not limited to people working on fur and poultry farms, official veterinarians and laboratory personnel at THL, Finnish Food Authority, Turku University (TY), Helsinki University (HY) and Helsinki University Hospital (HUS).

## Cohort 2

Some of the subjects of cohort 1 form a separate cohort 2. Study subjects for cohort 2 will include persons who previously belonged to the target group who received the H5N1 vaccine (ref. 3) in 2009 (pre-pandemic H5N1, inactivated, AS03-adjuvanted A/Indonesia/5/2005-like split virion vaccine, 3.75µg HA, GlaxoSmithKline), and/or 2011 (inactivated, adjuvant-free A/Vietnam/1203/2004-like whole virus H5N1 vaccine, 7.5µg HA, Baxter) and which also belong to the target group of the recommendation for the avian influenza vaccine.

## Cohort 3

The study population (cohort 3) will include healthcare personnel who participate in a separate clinical trial on immunogenicity against influenza vaccine, where pre- and post-vaccination samples have been collected during each season since 2017 ("Immune Responses to influenza vaccinations and viruses among health care personnel", conducted by THL and HUS, ClinicalTrials.gov Identifier: NCT03323112). New samples will not be obtained from these subjects, but the samples obtained in the separate trial will be used. Influenza vaccinations of health and social care professionals are part of statutory control of infectious diseases and patient safety.

## Recruitment of study subjects

To recruit persons who are potentially exposed to avian influenza virus in their work (cohort 1), THL cooperates with Finnish Food Authority and HUS. Finnish Food Authority has contact details of different target groups, like fur farmers and poultry farmers (who are asked to inform their workers), the veterinarians and laboratory personnel at Finnish Food Authority. Laboratory workers at THL and HUS, TY and HY can be contacted through these institutes (cohorts 1 and 2). The subjects in the cohort 3 will not be contacted, since the consent in the influenza trial covers the use of the samples in the current study.

If the target groups for avian influenza vaccination widen to new risk groups, means to contact the new groups will be searched. THL may also use media such as web pages, announcements and articles in local newspapers and magazines to increase awareness of the study among the population. Most fur farms are located in counties of South, Central or North Ostrobothnia, and the recruitment will focus to these areas.

THL will send recruitment material including an 1-page invitation letter, the full study information sheet and the Informed Consent Form (ICF) with study visit appointment instructions, either directly to the target groups or to the home addresses to those who have expressed interest to participate.

If the avian influenza vaccinations start so early that the study cannot recruit participants before the vaccinations, or only a small part of the target sample could be recruited before the start of avian influenza vaccinations, THL will apply for approval to identify from the national vaccination register the subjects who have already received the vaccine and send invitations to the home addresses of a random sample of these subjects, requested from the Population Information System of the Digital and Population Data Services Agency.

## Informed Consent

After receiving the invitation material including the full information sheets and examples of the ICF, the subjects will be encouraged to contact the study staff to ask questions and discuss the details. They will have time to consider their participation, before they make an appointment to the study visit. The recruitment material will be available in Finnish, Swedish or English language.

Informed consent will be obtained from the subjects in cohorts 1 and 2 before any study procedures are performed. The subject must be able to read and understand the information adequately.

A consent is not needed from the subjects in the cohort 3, since the consent obtained in the trial 'Immune Responses to influenza vaccinations and viruses among health care personnel', NCT03323112 covers the use of the samples to this purpose.

## Inclusion criteria for cohorts 1 and 2

- Age 18 to 65 years
- Belongs to the target group of the avian influenza vaccine
- Is planning to receive at least one dose of the avian influenza vaccine
- Is a native speaker of Finnish, Swedish or English
- Has given written informed consent
- Home address in Finland
- Is able to give samples 3 weeks after each vaccine dose and preferably also participate in the follow-up at 6 and 12 months
- Pregnant and lactating women can participate in the study.

## Exclusion criteria for cohorts 1 and 2

- Has any medical contraindications to influenza vaccination
- History of an anaphylactic (i.e. life-threatening) reaction to any of the constituents or trace residues of the vaccines (egg and chicken proteins, ovalbumin, kanamycin and neomycin sulphate, formaldehyde, hydrocortisone and cetyltrimethylammonium bromide).

## Study samples

The study samples will be collected in THL's laboratory and THL's partners laboratory centres, primarily in HUS Diagnostic Center, Nordlab, South Ostrobothnia Welfare Region Laboratory and Fimlab. Laboratory analyses on samples are carried out at THL, or at collaborators' laboratories.

Samples will be collected at 5 study visits during the first year. A serum sample (maximum 10 ml of blood) is collected from the subjects before the 1st vaccine dose, 21 days (18-24 days) after the 1st dose and 21 days (18-24 days) after the 2nd dose. Follow-up samples are scheduled 6 months and 12 months after the last vaccine dose. In addition, a blood sample (maximum 50 ml) is taken from a small number of subjects (maximum 150) for evaluation of cell-mediated immunity. A saliva sample can also be taken from these subjects (maximum 150) for examination of mucosal immunity. Additional serum samples (up to 50 ml) will be collected from a small group of subjects (maximum of 20, distinct from those providing samples for cell-mediated immunity evaluation) to support the development of laboratory methods for influenza and avian influenza. Cell and saliva samples are taken only from those recruited in the capital area (Uusimaa county). Follow-up samples, if feasible, can be collected for up to 10 years after the last vaccine dose.

| Visit number | Timing in relation to vaccination | Time window                                   |
|--------------|-----------------------------------|-----------------------------------------------|
| 1            | 0 sample                          | 0-60 days before vaccination                  |
| 2            | 1 mo                              | 18-24 days after 1st vaccine dose             |
| 3            | 1 mo                              | 18-24 days after 2 nd vaccine dose |
| 4            | 6 mo                              | 150-210 days after 2nd vaccine dose           |
| 5            | 12 mo                             | 330-390 days after 2nd vaccine dose           |

Follow-up samples may be collected annually for up to 10 years.

In alternative recruitment, persons who have already received the vaccine are invited to the study 18-24 days after the most recent vaccine dose (1st or 2nd dose).

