Virus circulation at the human-animal interface, as is demonstrated by the ongoing fur farm outbreaks, further increases the risk of emergence of a pandemic avian influenza virus. Due to Finland's exceptional epidemic situation and the increased risk of a pandemic, Ministry of Social Affairs and Health (STM) has made a decision to participate in the EU's joint vaccine procurement. AFLUNOV, manufactured by Seqirus, has been on the market since 2010, contains the H5N1 A/turkey/Turkey/1/2005 virus, which is a virus of the development line 2.2.1 [6]. Antigenically and genetically, the older vaccine virus differs from the currently circulating development line 2.3.4.4b H5 viruses, which is why the manufacturer is currently customizing the vaccine to the A/Astrakhan/3212/2020 (H5N8) strain, in which the H5 protein is almost identical to the H5 protein of circulating avian strains found in Finland. It is expected that a tailored vaccine would provide moderate to good protection against the circulating clade 2.3.4.4b viruses through cross-reactivity and protection. Cross-protection can be based on both antibody-mediated and cell-mediated immunity, which recognizes common structures of the vaccine virus and circulating viruses. However, it must be noted that influenza viruses are constantly changing as the virus multiplies, but also through reorganization of the virus's inheritance, which may result in a virus capable of circumventing the protection provided by the vaccine.

The vaccines were expected to be in use in the beginning of 2024, but due to delays in the registration process, vaccination was initiated only in June 2024. The target groups to be vaccinated were decided based on an updated risk assessment. The target groups include people working in fur farms and poultry industry, official veterinarians and laboratory workers or people working in the collection or analysis of bird influenza samples. In addition, the vaccine is offered to other persons

over the age of 18 who are at special risk, such as bird ringers. The vaccine is given in a series of two doses, where the second dose is given three weeks or later after the first dose.

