In a previously published study, it was found that the seasonal influenza vaccine produced neutralizing antibodies also against H5N1 viruses in a large proportion of the subjects, indicating the

existence of an antibody-dependent cross-reactivity [7]. At one month after seasonal influenza vaccination, 28/38 (74%) showed a >4-fold increase of neutralizing antibody titer measured with neutralization test, and 13/38 serum samples (34%) showed a 20-fold increase of neutralizing Abs against influenza H5N1. HI titers against H5N1 remained at undetectable levels after seasonal vaccination in 13/38 (34.2%) of donors [7]. Also, H5N1 virus-specific CD4 T cell responses (in small frequency) were detected in several persons at baseline, and vaccination with a seasonal influenza enhanced the frequency of H5N1 specific CD4 T cells [7]. At 1 month after seasonal influenza vaccination influenza H5N1 specific CD4 response was detectable in 41.6% of study participants. Another study reported that vaccination with seasonal influenza vaccine provided a partial protection against a lethal H5N1 challenge in mice, and it was suggested that seasonal influenza vaccination could be used as an interim measure to decrease morbidity and mortality from H5N1 prior to the availability of a specific vaccine [8]. Mouse experiments have also shown that non-neutralizing antibodies against HA epitopes produced by multiple immunizations with seasonal influenza vaccines that are at least in part directed against conserved HA epitopes, mediated protection from challenge with H5N1 even in the absence of detectable neutralizing antibodies against the H5N1 virus [9]. Based on these findings, it is possible that partial cross-reactivity, potentially even some cross-protection may be achieved with the seasonal influenza vaccine through both neutralizing and non-neutralizing antibodies, and T-cell-mediated immunity, at least in some of the vaccinated. Since the concentration of serum antibodies remains at its highest for about three months after vaccination, and since the proportion of potentially cross-reacting antibodies is relatively small, it would be expected that the effect (cross-reactivity and possible cross-protection) may last a relatively shorter time after vaccination.

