## Secondary objectives

To evaluate

1. humoral immune responses produced by the avian influenza vaccine against different H5N1 development lineages (clades) that have occurred before 2023, or that are identified to occur during the study

2. cellular immune responses induced by the customized avian influenza vaccine, against different H5N1 clades
3. the effects of prior seasonal influenza vaccinations on the immune responses induced by the avian influenza vaccine
4. humoral immunity produced by seasonal influenza vaccinations against different H5N1 lineages evaluated from samples collected from healthcare personnel belonging to the target group of the seasonal influenza vaccine (“Immune responses to influenza vaccinations and viruses among health care personnel”, ClinicalTrials.gov Identifier: NCT03323112)
5. humoral and cellular immune responses induced by the H5N1 2.3.4.4b customized vaccine in subjects who have previously received avian influenza vaccines
6. humoral and cellular immune responses induced by other respiratory or non-respiratory pathogens and vaccines against them, and their potential association with immune responses induced by seasonal and avian influenza vaccines or viruses

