### Exploratory objective

Development of laboratory methods for influenza and avian influenza

**Primary outcome measure:** Seroconversion proportion in all study subjects 3 weeks after the second dose given at least 21 days after the first dose, as assessed by the microneutralization test.

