### Secondary response variables:

- Rate of **seroconversion** defined as the percentage of subjects with either a pre-vaccination MNT titer  $< 1:10$  and a post vaccination MNT titer  $\geq 1:80$  or a pre-vaccination MNT titer  $\geq 1:10$  and a minimum four-fold rise in post-vaccination HI antibody titer.
- Geometric mean titers at pre- and post-vaccination.
- Detectable increase in T cell (CD4+ and CD8+) responses against H5N1 virus specific antigens in avian influenza virus vaccinated individuals.
- Geometric mean antibody titers and detectable T responses against other pathogens and/or vaccines of interest in the target group of the avian influenza virus vaccine.

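### The primary outcome does not separate subjects who receive a seasonal influenza dose between the baseline and visit-3 samples, so a seasonal-induced H5N1 rise can count as avian-vaccine seroconversion

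*Protocol*

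**What the plan says.** The primary outcome, stated under Exploratory objective, is "Seroconversion proportion in all study subjects 3 weeks after the second dose given at least 21 days after the first dose", measured by microneutralisation (MNT). Under Secondary response variables, seroconversion depends only on titres: a baseline MNT titre below 1:10 followed by at least 1:80, or a baseline of 1:10 or more "and a minimum four-fold rise in post-vaccination HI antibody titer".

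Three rules set the length of the measured interval:
- the baseline window in Study samples, "0-60 days before vaccination";
- the dosing rule in the Introduction, "the second dose is given three weeks or later after the first dose", with no upper limit;
- the visit-3 window in Study samples, "21 days (18-24 days) after the 2nd dose".

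The Study design section adds: "No control arm is included in this study".

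On seasonal vaccine, the Abstract says it has been recommended to fur farm workers and other risk groups since September 2023, that the avian vaccine is offered to the same target groups, and that the 2023 seasonal distribution ran from October through November. The Seroprotection section cites a 38-person study of seasonal vaccine in which 28/38 (74%) had a more than four-fold rise in H5N1 neutralising titre and "13/38 serum samples (34%) showed a 20-fold increase of neutralizing Abs against influenza H5N1". Secondary objective 3 is to evaluate "the effects of prior seasonal influenza vaccinations on the immune responses induced by the avian influenza vaccine". The data collection section takes seasonal vaccinations from the national register for the study period and the preceding five years.

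**The concern.** The measured change is meant to describe the response to the avian vaccine. A seasonal dose given after the baseline sample and before visit 3 falls inside that change. If it raises the H5N1 titre enough to meet the definition, the subject is counted as an avian-vaccine seroconverter, and a single-arm design cannot show otherwise. The rise in GMT is exposed in the same way.

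Overlap is foreseeable. According to the Abstract, seasonal vaccine was to precede avian vaccine by one to three months, but licensing delays moved the avian campaign to mid-2024. The current protocol version is dated 28 October 2024, so subjects enrolled in autumn could have both vaccines close together if later seasons follow the 2023 calendar.

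Objective 3 has a related problem. The Abstract frames the exposure as seasonal vaccine received before the avian vaccine. That puts two different situations in one group. A dose before the baseline sample has its rise already in the baseline titre. A dose between the baseline sample and dose 1 has its rise inside the measured change. A seasonal dose after dose 1 is not clearly covered at all.

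**Working it through.** **Length of the interval.** Time from baseline to visit 3 = B + D + V, with B = 0-60 days (baseline window), D ≥ 21 days (dose interval) and V = 18-24 days (visit-3 window).
- B = 0, D = 21: 39 to 45 days.
- B = 60, D = 21: 60 + 21 + 18 = 99 to 60 + 21 + 24 = 105 days.
- D has no upper limit, so neither has the interval.

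The 60-day window therefore lengthens the exposure but does not create it.

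**The plan's own figure.** The Sample size section uses n = Z²p(1−p)/E² with Z = 1.96, p = 0.75 and E = 0.05. This gives 3.8416 × 0.1875 / 0.0025 = 288.12, which agrees with the stated 288 (target 300). The criterion in Study hypothesis is a lower 95% limit of at least 70%, so the plan works with a 5-point distance between the assumed rate and the threshold.

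**Which cited figure fits the definition.** A subject below 1:10 must reach 1:80. A four-fold rise from below 10 stays below 40 and does not qualify. A 20-fold rise reaches 80 from any starting value of 4 or more (80/20 = 4). A subject at 1:10 or above is judged, as written, on HI titre, which the neutralisation figures do not describe. The Introduction calls population immunity to avian influenza viruses low or absent, so most subjects should start below 1:10. The 34% figure is thus the closer guide, and the 74% figure does not apply to most subjects.

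**Size.** Let p be the true avian-vaccine rate, q the share with a seasonal dose in the interval, and s the chance that the seasonal dose alone meets the definition. Under independence:

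bias = (1 − p) × q × s.

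The protocol gives no q, so 10-50% is assumed, with s = 0.34. The chance of meeting the criterion assumes 300 evaluable subjects, of whom 226 must seroconvert for the Clopper-Pearson lower limit to reach 70%.

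| True rate p | Uptake q | Bias (points) | Chance without bias | Chance with bias |
|---|---|---|---|---|
| 75% | 10% | 0.25 × 0.10 × 0.34 = +0.85 | 47.8% | 61.3% |
| 75% | 25% | 0.25 × 0.25 × 0.34 = +2.1 | 47.8% | 79.2% |
| 75% | 50% | 0.25 × 0.50 × 0.34 = +4.25 | 47.8% | 95.7% |
| 70% | 10% | 0.30 × 0.10 × 0.34 = +1.0 | 2.4% | 5.5% |
| 70% | 25% | 0.30 × 0.25 × 0.34 = +2.55 | 2.4% | 15.5% |
| 70% | 50% | 0.30 × 0.50 × 0.34 = +5.1 | 2.4% | 49.4% |

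Lifting a true 70% to an observed 75% needs q × s = 0.05/0.30 = 0.167, that is, q of about 49% when s = 0.34.

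**The case against.** **It belongs in the SAP.** A flag and a restricted analysis are often left to a statistical analysis plan, which is not at hand. This stands in part, and such an analysis may exist. But the primary population, the sampling windows, the endpoint definition and the exposure in objective 3 are fixed in the protocol, and the problem comes from these.

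**Seasonal vaccination is not ignored.** A reader might infer that the protocol makes no provision for it at all. The documents do not support that. Register dates are collected, objective 3 studies prior seasonal vaccination, and objective 4 with cohort 3 measures H5N1 responses in sera taken before and after seasonal vaccination. Cohort 3 is not a concurrent control, but it can show how far seasonal vaccine alone raises these titres. None of this says how an affected subject counts in the primary outcome.

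**The size could be much smaller, or nil.** Uptake in the interval is not stated. Subjects who received dose 1 in June or July 2024 at the minimum dose interval would have reached visit 3 by mid-September, before an October-November seasonal campaign. The cited rises come from one study of 38 people, and the protocol itself expects the share of cross-reacting antibody to be relatively small. If poor responders to one vaccine are also poor responders to the other, independence overstates the bias. This stands.

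**The direction is not certain.** A reader might infer a proven upward bias, perhaps above 9 points by applying the 74% figure (0.25 × 0.50 × 0.74 = 9.25). That figure does not fit the definition for most subjects, and the Introduction says vaccination history may have unknown effects on later vaccine responses, so interference could pull the other way.

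**The seroprotection criterion uses no baseline.** A post-vaccination MNT titre of at least 80 does not depend on when baseline was drawn. This is correct, and the point about baseline timing concerns seroconversion and the GMT rise.

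**Conclusion.** The point holds as a gap in how the primary outcome and objective 3 are specified. Followed as written, the protocol can credit an H5N1 rise from an intervening seasonal dose to the avian vaccine, and it places seasonal doses from before and after the baseline sample in one exposure group.

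The likely effect on the primary proportion is about +0.9 to +4.3 points. This assumes 10-50% uptake in the interval, a true rate of 75%, s = 0.34 and independence. Uptake is assumed, not documented, and interference could reduce or offset the effect. The upper part of the range is close to the 5-point margin on which the sample size rests, so it could influence whether the 70% criterion is met. The documents do not show that it will.

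A reader might also blame the 60-day baseline window alone. The interval is at least 39 days without it, so shortening the window would reduce the exposure but not remove it. This is an inexpensive improvement to the plan, not a defect that undermines the trial.

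**What to change.** 1. From the register dates already collected, derive a flag for any seasonal influenza dose between the visit-1 and visit-3 samples.
2. State in the protocol that the primary proportion and the GMT rise are reported for all subjects and again without flagged subjects, and report how many are flagged.
3. In objective 3, classify seasonal exposure as before the baseline sample, between the baseline and visit-3 samples, or none.
4. Use the cohort 3 results to indicate how large a seasonal-only H5N1 rise to expect when reading the difference between the two analyses.

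Nobody's vaccination timing changes, and no new data are needed.

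The cost is one derived variable, one additional analysis and some precision in the restricted result. At a rate of 75%, the half-width 1.96 × √(0.1875/n) is 4.9 points with 300 subjects, 5.2 with 270 (10% flagged) and 6.9 with 150 (50% flagged). Flagged subjects may also differ from the rest in occupation or enrolment month, so the restricted result should be read beside the full one and not in place of it.
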